## Methods and design

RiMINI is a monocentric exploratory pilot study on 60 patients with MHE as assessed by critical flicker frequency (CFF) analysis. Additionally, visual evoked potentials’ (VEP) testing, electroencephalography (EEG) and a psychometric test (NCT-A) will be carried out. The patients will be randomized to treatment either with rifaximin alone 550 mg twice daily (bid) continuously for a period of 3 months or to continuous treatment with 550 mg rifaximin bid in combination with lactulose 30–60 ml daily (to pass 2–3 semisoft stools/day) for 3 months. An esophagogastroduodenoscopy (EGD) will be performed at baseline, at the end of antibiotic treatment, as well as 6 and 12 weeks after the end of treatment to obtain gastric and duodenal biopsies and aspirates will be taken. The samples will be analyzed for their specific bacterial taxae by applying next generation sequencing (NGS) after ribonucleic acid (RNA) isolation. Additionally, stool samples will be taken at the same time points. Prevalence of *Helicobacter pylori*, which is the predominant gastric microbe, will be assessed by histology, rapid urease test and serology at study entry. For clinical assessment, quantification of MHE and therapeutic effects, CFF, EEG, VEP and psychometric tests are assessed weekly during the first month and every 4 weeks from the beginning of the second month until the end of the post-treatment follow-up.

Changes in the gut microbiome from antibiotic therapy with rifaximin alone or rifaximin with lactulose are analyzed comparing pre- and post-antibiotic time points. The follow-up data will show whether the change in the gut microbiome is persistent or transient. We will compare the effect of antibiotic therapy with rifaximin alone with a combination therapy with lactulose on the clinical course of MHE. As planned, NGS methods (Illumina sequencing, Illumina, San Diego, CA, USA) will be used to characterize the composition and changes of both stomach and small bowel microbiomes. Bacterial ribosomal ribonucleic acid (rRNA) will be isolated from aspirates, biopsies and feces and then stored in RNAlater at −80 °C. The samples will be analyzed by NGS methods as described below with the aim of identifying the microbiome of the stomach and the small bowel, as well as of the large bowel, in patients with liver cirrhosis and MHE and its changes before and after therapy (Fig. 1).

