### Schedule of evaluations/Estimated timelines

This study consists of three phases: (1) the screening phase, (2) the treatment phase and (3) the follow-up phase (Table 1).

**Table 1 Tab1:** Clinical treatment plan

	Inclusion into study	Screening	Assignment to treatment group	Treatment phase	EOT	6 weeks after EOT	12 weeks after EOT = End of study
Time		Day −15 –day 0	0 (visit 0)	Days 1–90 (visits 1–3) −3d to +3d	Visit 3	Day 129– day 135 (visit 5) −3d to +3d	Day 171– day 177 (visit 6) −3d to +3d
Informed consent	x						
Demographics		X					
Medical history concomitant medication		X		x	X	x	X
Physical exam, vital signs, weight		X	x	x	X	x	X
ECG		X					
ECOG performance status and QOL assessment		X	x	x	X	x	X
Blood tests including pregnancy test		X	x	x	X	x	X
EGD with biopsies			x		X	x	X
	Inclusion into study	Screening	Assignment to treatment group	Treatment phase	EOT	6 weeks after EOT	12 weeks after EOT = End of study
Time		Day −15–day 0	0 (visit 0)	Days 1–90 (visits 1–3) −3d to +3d	Visit 3	Day 129– day 135 (visit 5) −3d to +3d	Day 171– day 177 (visit 6) −3d to +3d
*H. pylori* serology			x				
Stool samples			x	x	x	x	x
Rapid urease test			x				
Assessment of neurocognitive function (NCT-A, CFF, VEP, EEG)		X		Days 1–28 weekly, then every 4 weeks	>x	x	x

*CFF* critical flicker frequency, *ECG* electrocardiogram *ECOG* Eastern Cooperative Oncology group, *EEG* electroencephalogram, *EGD* esophagogastroduodenoscopy, *EOT* end of treatment, *NCT-A* number-connection test A, *QOL* quality of life, *VEP* visual evoked potentials

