### Randomization procedure

The randomization will be performed with the clinical database software secuTrial that is also used for the data management in the study. The two arms will be randomized in a 1:1 ratio using the minimization method described by Pocock and Simon with a stratification for age and gender.

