### Statistical analysis

All demographic and baseline variables are presented in descriptive statistics stratified by treatment arm in the full analysis set (FAS, all randomized patients). Exploratory tests, according to the level of the respective variables, will search for differences between both arms which might occur despite randomization. The primary target variable is compared between both treatment arms. The odds ratio for treatment success is calculated between both treatment arms together with the corresponding two-sided 95 % confidence interval. If the confidence interval is completely above or below the threshold of 1, the superiority of the corresponding treatment arm with larger success rates can be concluded. If the confidence interval covers the threshold of 1, then the lower and upper confidence limits give limits which can be used in non-inferiority statements. This analysis is performed primarily in the modified full analysis set (MFAS, all randomized patients but excluding those with missing CFF tests) according to the ITT principle. Missing values are imputed by the last observation carried forward principle.

Secondary analyses for the primary target variable include (1) logistic regression analysis with treatment arm, sex, age and baseline value of CFF as co-variables, (2) analog analyses in the per protocol set (PPS, patients of the MFAS excluding those with severe protocol violations), (3) analog analyses for the result of CFF at end of follow-up, (4) description of the results of the psychometric tests (mean and standard deviation) per treatment arm and comparison in two-sample *t* tests (both at end of treatment and end of follow-up).

The secondary efficacy variables are compared between the treatment arms in analysis of covariance (ANCOVA) models with treatment arm, sex, age and respective baseline variable as factors or co-variables, respectively.

Safety analysis is done in the safety set (SS, patients receiving at least one treatment) in descriptive and exploratory analyses. Laboratory variables and rates of SAEs are compared between both treatment arms using the Mann-Whitney *U* test and Fisher’s exact test.

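### The laboratory safety comparison names no baseline term, although baseline bloods are collected: a valid test, but less efficient than it could be at no cost

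*Protocol article*

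**What the plan says.** The last paragraph of Statistical analysis in the protocol article covers safety. It sets the status of the analysis: "Safety analysis is done in the safety set (SS, patients receiving at least one treatment) in descriptive and exploratory analyses". It then names the tests: "Laboratory variables and rates of SAEs are compared between both treatment arms using the Mann-Whitney" U test and Fisher's exact test. The natural reading is Mann-Whitney for laboratory variables and Fisher for SAE rates. No covariate is named for the laboratory comparison. The text does not say whether post-treatment values or changes from baseline are compared, or at which visit.

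The preceding paragraph treats efficacy differently: "The secondary efficacy variables are compared between the treatment arms in analysis of covariance (ANCOVA) models". Besides the arm, those models contain sex, age and the entry value of the variable concerned.

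Baseline laboratory values will exist. In Table 1 the row "Blood tests including pregnancy test" is marked at screening, at assignment to treatment (visit 0), in the treatment phase, at end of treatment, and 6 and 12 weeks later.

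On size: "RiMINI is a monocentric exploratory pilot study on 60 patients with MHE", and "The two arms will be randomized in a 1:1 ratio using the minimization method". That is about 30 per arm before dropout.

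**The concern.** A two-group rank test on post-treatment values carries all the between-patient variation that was already present at entry. Where a patient's entry value predicts the later one, part of that variation can be removed by putting the entry value in the model. The plan does this for the secondary efficacy variables and names no such step for the laboratory variables. Minimization uses age and gender only, so entry laboratory values are balanced only by chance.

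What is at stake is precision. In a pilot of fixed size, whose results are meant to support planning of a later confirmatory trial (Power analysis section), a moderate laboratory difference between the arms may go unnoticed when the data already collected could have shown it.

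**Working it through.** The article gives no laboratory shift of interest, SD, baseline correlation or power, so there is no figure of its own to reproduce.

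**Inputs from the article:** 60 patients, 1:1, so n = 30 per arm; Mann-Whitney for laboratory variables; bloods at visit 0.

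**Assumptions, not in the article:** two-sided alpha of 0.05 (the article states a "two-sided 95 % confidence interval" only for the primary odds ratio); true shift 0.3 to 1.0 SD; baseline correlation r = 0.3 to 0.8; Mann-Whitney efficiency of 0.955 with normal data, so an effective n of 30 × 0.955 = 28.65.

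**Step 1. Rank test on post-treatment values.** Power = Φ(d / √(2/28.65) − 1.96), with √(2/28.65) = 0.264.

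- d = 0.3: 21%
- d = 0.5: 0.5/0.264 = 1.89; Φ(−0.07) = 47%
- d = 0.65: 69%
- d = 0.8: 86%
- d = 1.0: 97%

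Power reaches 50% at 1.96 × 0.264 = 0.52 SD and 80% at (1.96 + 0.84) × 0.264 = 0.74 SD.

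**Step 2. Baseline as covariate.** The residual SD falls to √(1 − r²). The shift detectable with 80% power is 2.80 × √(2/30) × √(1 − r²): 0.69 SD at r = 0.3, 0.63 at 0.5, 0.52 at 0.7 and 0.43 at 0.8. At r = 0.7 the residual variance is 1 − 0.49 = 0.51, so adjustment is worth nearly a doubling of the sample.

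**Step 3. Rank test on changes from baseline.** The SD of a change is √(2(1 − r)). This is below 1 only when r exceeds 0.5, so change scores help at high correlation and hurt at low correlation.

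**Step 4. Simulation.** 30 per arm, 0.5 SD shift, 2000 runs per setting; Monte Carlo standard error about √(0.45 × 0.55/2000) = 1.1 points. Rank ANCOVA regresses the ranked outcome on arm and ranked baseline. Normal data:

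| r | Mann-Whitney, post values | Mann-Whitney, change | Rank ANCOVA | Gain over post values | Gain over change |
|---|---|---|---|---|---|
| 0.3 | 44.4% | 33.4% | 48.1% | 3.7 | 14.7 |
| 0.5 | 44.0% | 45.3% | 54.7% | 10.7 | 9.4 |
| 0.7 | 45.7% | 67.8% | 71.2% | 25.5 | 3.4 |
| 0.8 | 45.2% | 82.0% | 83.0% | 37.8 | 1.0 |

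**Step 5. Larger shifts.** At 0.8 SD, Mann-Whitney on post values has 83% to 84% power and rank ANCOVA 86% to nearly 100%. At 0.75 SD, Mann-Whitney on post values has about 78%.

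**Step 6. Skewed values.** With lognormal data and a 0.5 SD shift on the log scale, Mann-Whitney on post values stays near 45%. ANCOVA on raw values gives 37%, 37%, 51% and 61% over the four correlations. Rank ANCOVA gives 50%, 56%, 72% and 83%. The scale therefore matters: ranks or logs, not raw values.

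**Step 7. Type I error.** With no true shift, all methods rejected in 3.8% to 5.6% of runs.

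**The case against.** The strongest reply is that the article states nothing wrong. A Mann-Whitney test is valid in a randomized comparison, costs about 5% efficiency with normal data, and suits skewed laboratory values, where ANCOVA on raw values can do worse at low correlation. Using ANCOVA for efficacy does not oblige its use in a laboratory comparison labelled descriptive and exploratory, so there is no contradiction. No decision rule hangs on the p-value. Adverse events are graded separately by NCI-CTCAE and SAE rates have their own test. All of this stands, and it is why the point is only an improvement.

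A second reply is that the absence of baseline adjustment is partly inferred, since the test may be meant for changes from baseline. That also stands. It shrinks the gain to 3.4 points at r = 0.7 and 1.0 point at r = 0.8. It does not remove the case, because at r = 0.3 the change-score test falls to 33%, below the same test on post-treatment values, and rank ANCOVA avoids that risk.

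A reader might infer something stronger: that real laboratory shifts will generally be missed, or that a finding of no difference is likely whatever the truth. The documents do not support this. They name no shift of interest, and the test detects shifts above about half an SD more often than not. A reader might also suppose that in cirrhosis the spread between patients swamps any treatment-related change, so that the comparison mostly shows who was sicker at entry. The documents give no figure for either quantity. In a randomized comparison that spread adds noise, not systematic bias.

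For small shifts the main limit is the sample size: at 0.3 SD even normal-theory ANCOVA with r = 0.8 has only 49% power.

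**Conclusion.** The point holds as a free gain in efficiency. The stated laboratory comparison is a valid rank test with no baseline term named, while the baseline values are collected and used in the same way elsewhere in the section. At an assumed shift of 0.5 SD with about 30 per arm and two-sided 0.05, power is about 45% on post-treatment values, against about 48% to 83% for rank ANCOVA at assumed correlations of 0.3 to 0.8. The benefit is slight at the low end of that range and substantial from about r = 0.7. It nearly vanishes at r of 0.7 or more if changes from baseline are what will be tested. Dropout would lower every power figure. No conclusion of the trial is invalidated.

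**What to change.** In the safety paragraph, compare laboratory variables between arms by ANCOVA on ranks or on log values, with treatment arm and the visit 0 value as covariate. Keep the Mann-Whitney test as a descriptive supplement if wanted, and say whether it uses post-treatment values or changes from baseline. Fisher's exact test for SAE rates is unaffected.

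The cost is one changed sentence and one changed line of analysis code. The values are already scheduled in Table 1, so no extra visits, samples or patients are needed. Because the study is open label and already recruiting, the change should be fixed before laboratory values are compared by arm.

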### Power analysis

This is an exploratory pilot study as so far data on the monotherapeutic effect of rifaximin in the treatment of MHE are scarce. The results will give the basis for planning a later confirmatory multicenter trial. With the given sample sizes the proof of differences between the two treatment options, or of acceptable non-inferiority margins, can be expected only if the additional of lactulose drastically improves the success rates of the rifaximin treatment.

### Ethics

The planning and conduct of this clinical study are subject to national laws. The study will be conducted in accordance with the protocol and the ethical principles that have their origin in the Declaration of Helsinki and the International Conference on Harmonization guidelines for Good Clinical Practice (ICH-GCP) [20, 21].

The study protocol and any amendments have been reviewed and approved by the ethic committee of the Otto-von-Guericke University of Magdeburg, Germany, and by the competent authority, BfArM, before implementation.

### Data handling, data processing, monitoring and auditing

Data required according to this protocol are to be recorded in the eCRFs in a timely manner. A Data Manual (DM) will be maintained specifying all relevant aspects of data processing for the study (including data validation, cleaning, correcting, releasing).

For data coding (e.g., AEs, baseline findings, medication, medical/surgical history), internationally recognized and accepted dictionaries will be used.

All monitoring activities will be overseen by the coordinating study bureau. A member of the sponsor’s (or designated chief research officer’s (CRO’s) quality assurance unit may visit the investigator annually in order to audit the performance of the study at the study site and the study documents originating there.

In addition, inspections by health authority representatives – including foreign authorities – and Institutional Ethical Committees (IECs) and Institutional Review Boards (IRBs) are possible at any time.

## Discussion

Rifaximin treatment for patients with overt HE has been shown to be effective in the amelioration of cognitive function and in the prevention of recurrence of overt HE [14]. In patients with MHE rifaximin significantly improves cognitive function and HRQL [13, 14]. However, more than 90 % of patients with HE treated in prospective studies received a combination therapy of rifaximin and lactulose. Only a single prospective trial with a limited number of subjects addressed the effect of rifaximin on MHE [13]. The primary objective of our study, therefore, is to analyze the efficacy of rifaximin alone or in combination with lactulose on the improvement of neuropsychometric and neurophysiological changes in patients with MHE. Although current therapeutic concepts in the treatment of HE are directed to reduce bacterial ammonia production by antibiotic treatment, the role and contribution of the upper-GI microbiota in the pathogenesis of HE remain poorly understood. The secondary objective of this study aims at evaluating the microbial diversity and the composition of the microbiota in the upper GI tract, and in the stool, in cirrhotic patients with and without MHE before, during, and after therapy to assess the degree of changes and whether they are transient or persistent.

## Trial status

This trial is currently recruiting patients. The first patient was randomized on 24 April 2015.

## Abbreviations

AE: adverse event
cDNA: complementary deoxyribonucleic acid
CFF: critical flicker frequency
CRO: chief research officer
DM: Data Manual
DNA: deoxyribonucleic acid
dsDNA: double-stranded deoxyribonucleic acid
DSUR: development update safety report
eCRF: electronic Case Report Form
EEG: electroencephalography
EGD: esophagogastroduodenoscopy
ERC: endoscopic retrograde cholangiography
FAS: full analysis set
HE: hepatic encephalopathy
HRQL: health-related quality of life
IEC: Institutional Ethical Committee
IRB: Institutional Review Board
MFAS: modified full analysis set
MHE: minimal hepatic encephalopathy
NCT-A: number- connection test A
NGS: next generation sequencing
PCR: polymerase chain reaction
PPS: per protocol set
RNA: ribonucleic acid
rRNA: ribosomal ribonucleic acid
SAE: severe adverse event
SS: safety set
VEP: visual evoked potentials
